## Capecitabine (or 5FU) dose non-haematological modifications

Toxicity due to capecitabine administration may be managed by symptomatic treatment and/or modification of the dose (treatment interruption or dose reduction). Once the dose has been reduced, it should not be increased at a later time. Patients taking capecitabine should be informed of the need to interrupt treatment immediately if moderate or worse toxicity occurs. Doses of capecitabine omitted for toxicity are not replaced or restored, instead patients should resume the planned treatment cycle. The following are the recommended dose modifications for toxicity. In addition patients should receive loperamide in case of diarrhoea, pyridoxine for PPE and mouthwashes and anti-emetics according to local policy

**Toxicities should be graded according to CTCAEv3.0. An abridged version is included in Appendix XI for use when completing CRFs. In particular, diarrhoea, nausea, vomiting, stomatitis and skin reactions are to be noted.**

**Please use alternative specific toxicity for Hand-foot syndrome (PPE), the frequency of which in patients receiving capecitabine has led to altered toxicity ratings.**

| Grade of hand-foot syndrome |                                                                                                                                                                                                  |
|-----------------------------|--------------------------------------------------------------------------------------------------------------------------------------------------------------------------------------------------|
| 1                           | Numbness, dysaesthesia/paraesthesia, tingling, painless swelling or erythema of the hands and/or feet and/or discomfort which does not disrupt the patient's normal activities.                  |
| 2                           | Painful erythema and swelling of the hands and/or feet and/or discomfort affecting the patient's activities of daily living.                                                                     |
| 3                           | Moist desquamation, ulceration, blistering and severe pain of the hands and/or feet and/or severe discomfort that causes the patient to be unable to work or perform activities of daily living. |

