### 12.2 Outcome measures

#### Stage 1:

The primary outcome measure is treatment failure rate in the research arm. Treatment failure rate will be assessed at 24 weeks (12 weeks after completion of CRT) and is defined as pathologically confirmed (by endoscopic assessment and/or biopsy) residual disease and/or CT scan of thorax and abdomen showing progressive disease according to RECIST criteria.

The secondary outcome measures are: toxicity and feasibility.

- **Toxicity:** will be scored using the NCI CTCAE v3.0 and RTOG acute radiation morbidity scoring criteria (Appendix XII) at baseline, during treatment and at pre-specified time points on follow-up. Serious adverse events will be monitored “real-time” by the Chief Investigator and TMG.
- **Feasibility:** will be measured through the number of protocol dose modifications and delays.

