#### Stage 2:

The primary outcome measure is overall survival (OS). Overall survival is calculated from the date of randomisation to death from any cause. Those patients still alive will be censored at the date last seen.

The secondary outcome measures are: Toxicity, quality of life, quality assurance and health economics.

- **Toxicity:** will be scored using the NCI CTCAE v3.0 and RTOG acute radiation morbidity scoring criteria at baseline, during treatment and at pre-specified time points on follow-up. Serious adverse events will be monitored “real-time” by the Chief Investigator and TMG.
- **Quality of Life (QoL):** will be documented through the use of EORTC-C30 plus oesophageal specific modules (OES18) and dermatology life quality index (DLQI) at baseline, during treatment and at pre-specified time points on follow-up.
- **Quality assurance (QA):** A detailed QA program will be in place to ensure adherence to the protocol (please see separate radiotherapy protocol). Major and minor deviations will be collected.

- **Health Economics (HE):** HE analysis will be performed using appropriate data collected on the CRFs, from relevant cost and resource utilisation data collected from finance and clinical staff, from administration of EQ-5D at baseline, during treatment and at pre-specified time points on follow-up.

NB: Although activity, safety and feasibility will not be formally assessed in the control arm in Stage 1, the randomisation of patients will continue using the same process and on a 1:1 allocation and therefore those patients in Stage 1 will be included in the analysis of Stage 2.

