| Wound complication, non-infectious                          | Incisional separation of ≤25% of wound, no deeper than superficial fascia                        | Incisional separation of > 25% of wound with local care, asymptomatic hernia                                                                                 | Symptomatic hernia without evidence of strangulation; fascial disruption/dehiscence without evisceration; primary wound closure or revision by operative intervention indicated; hospitalization or hyperbaric O 2 therapy indicated | Symptomatic hernia with evidence of strangulation; fascial disruption with evisceration; major reconstruction flap, grafting, resection or amputation indicated |
| Diarrhoea                                                   | Increase of <4 stools per day over baseline; mild increase in ostomy output compared to baseline | Increase of 4-6 stools per day over baseline; IV fluids indicated <24 hrs; moderate increase in ostomy output compared to baseline; not interfering with ADL | Increase of ≥ 7 stools per day over baseline; incontinence; IV fluids <24 hrs; hospitalisation; severe increase in ostomy output compare to baseline; interfering with ADL                                                                      | Life-threatening consequences (e.g. hemodynamic collapse)                                                                                                       |
| Dysphagia                                                   | Symptomatic, able to eat regular diet                                                            | Symptomatic and altered eating/swallowing (e.g. altered dietary habits, oral supplements); IV fluids indicated <24 hrs                                       | Symptomatic and severely altered eating/swallowing (e.g. inadequate oral caloric or fluid intake); IV fluids, tube feedings, or TPN indicated ≥24 hrs                                                                                           | Life-threatening consequences (e.g. obstruction, perforation)                                                                                                   |

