| Thrombosis/ thrombus/ embolism | -                                                                              | Deep vein thrombosis or cardiac thrombosis; intervention (e.g., anticoagulation, lysis, filter, invasive procedure) not indicated                                                            | Deep vein thrombosis or cardiac thrombosis; intervention (e.g., anticoagulation, lysis, filter, invasive procedure) not indicated                                                                                                                                  | Embolic event including pulmonary embolism or life threatening thrombus                      |

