## APPENDIX XII

### RTOG/EORTC LATE RADIATION MORBIDITY SCORING SCHEMA

|                     | 0    | 1                                                                                                            | 2                                                                                                                           | 3                                                                                                                                        | 4                                                                             |
|---------------------|------|--------------------------------------------------------------------------------------------------------------|-----------------------------------------------------------------------------------------------------------------------------|------------------------------------------------------------------------------------------------------------------------------------------|-------------------------------------------------------------------------------|
| Skin                | None | Slight atrophy
Pigmentation change
Some hair loss                                                      | Patch atrophy;
Moderate telangiectasia;
Total hair loss                                                               | Marked atrophy;
Gross telangiectasia                                                                                                  | Ulceration                                                                    |
| Subcutaneous Tissue | None | Slight induration (fibrosis) and loss of subcutaneous fat                                                    | Moderate fibrosis but asymptomatic
Slight field contracture <10% linear reduction                                        | Severe induration and loss of subcutaneous tissue
Filed contracture >10% linear measurement                                           | Necrosis                                                                      |

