| Bladder                 | None | Slight epithelial atrophy
Minor telangiectasia (microscopic hematuria)                             | Moderate frequency
Generalized telangiectasia
Intermittent macroscopic hematuria                          | Severe frequency and dysuria
Severe generalized telangiectasia (often with petechiae)
Frequent hematuria
Reduction in bladder capacity (<150 cc) | Necrosis/ Contracted bladder (capacity <100 cc)
Severe hemorrhagic cystitis |
| Bone                    | None | Asymptomatic
No growth retardation
Reduced bone density                                         | Moderate pain or tenderness
Growth retardation
Irregular bone sclerosis                                   | Severe pain or tenderness
Complete arrest of bone growth
Dense bone sclerosis                                                                       | Necrosis/
Spontaneous fracture                                              |
| Joint                   | None | Mild joint stiffness
Slight limitation of movement                                                 | Moderate stiffness
Intermittent or moderate joint pain
Moderate limitation of movement                    | Severe joint stiffness
Pain with severe limitation of movement                                                                                         | Necrosis/ Complete fixation                                                    |

GUIDELINES from <http://www.rtog.org/members/toxicity/late.html>

All toxicities Grade 3, 4 or 5\* must be verified by the Principal Investigator.

\* ANY TOXICITY WHICH CAUSED DEATH IS GRADED 5.

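### The RTOG acute toxicity criteria are referred to an appendix that holds the late-effects schema, and two rows of the abridged CTCAE table for CRFs do not cleanly separate grade 2 from grade 3

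*Protocol*

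**What the plan says.** Section 12.2 names two instruments for Stage 1 toxicity and gives an appendix for the second: CTCAE v3.0 and "RTOG acute radiation morbidity scoring criteria (Appendix XII) at baseline, during treatment and at pre-specified time points on follow-up". The Stage 2 paragraph of the same section repeats the instruments without citing an appendix: "will be scored using the NCI CTCAE v3.0 and RTOG acute radiation morbidity scoring criteria at baseline, during treatment".

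Appendix XII is headed "RTOG/EORTC LATE RADIATION MORBIDITY SCORING SCHEMA" and closes with its source, "GUIDELINES from <http://www.rtog.org/members/toxicity/late.html>".

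For CTCAE v3.0, section 8.4.1 says of the grading table that "An abridged version is included in Appendix XI for use when completing CRFs". In that table the thrombosis row reads "Deep vein thrombosis or cardiac thrombosis; intervention (e.g., anticoagulation, lysis, filter, invasive procedure) not indicated" at grade 2, and exactly the same at grade 3. The diarrhoea row at grade 3 includes "IV fluids <24 hrs; hospitalisation; severe increase in ostomy output compare to baseline; interfering with ADL"; its grade 2 cell also limits IV fluids to under 24 hours.

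Section 11 requires CTCAE v3.0 for grading adverse events. It sends adverse reactions of grade 1 or 2 to the CRF toxicity form only, and those of grade 3 to 5 to an SAE form as well.

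**The concern.** Toxicity is an outcome in both stages. Section 12.3 has the IDMC review it, together with feasibility, before endorsing Stage 2, and section 1.2 says that recruitment stops if the findings are unacceptable. No numerical toxicity limit is given, so the judgement depends on grades being assigned in the same way across sites and arms.

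Three things in the grading material work against that. The reference for acute radiation scoring leads to a table of late effects. One row of the table supplied for CRFs has two grades that cannot be told apart. Another row has one criterion that does not change between grades.

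The events are foreseeable. Thrombosis is in the section 11 list of expected cisplatin effects, and the single-centre series in Table 1 (section 2.3) records one DVT among 31 oesophageal patients. Diarrhoea is among the toxicities that section 8.4.1 asks sites to note in particular, and section 14 expects it to be worse in the cetuximab arm.

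**Working it through.** This is a comparison of texts. The plan states no figure to reproduce.

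**1. Which scale is Appendix XII?** Three places agree that it is the late scale: the contents entry, the appendix heading and the source link. The items agree too: atrophy, telangiectasia, fibrosis, necrosis. The reference in section 12.2 therefore points to the wrong scale, and this cannot be a fault in reading the PDF. None of the fourteen appendices contains an RTOG acute schema. Section 12.2 also applies the acute criteria at follow-up and never mentions the late schema, although the schedule in section 5.5 continues toxicity assessment to month 60. So the section gives no rule for when the late table applies.

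**2. Thrombosis in Appendix XI.** Grade 1 is blank, grades 2 and 3 are the same text, and grade 4 covers embolic or life-threatening events. Both middle cells describe a thrombosis for which intervention is *not* indicated.
- Untreated DVT: fits grade 2 and grade 3 equally.
- DVT given anticoagulation, not embolic or life-threatening: fits neither.

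Which of the two cells is faulty cannot be settled from the protocol alone.

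**3. Diarrhoea in Appendix XI.** Six rows use the duration of IV fluids at both grades:

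| Row | Grade 2 | Grade 3 |
|---|---|---|
| Dysphagia | <24 h | ≥24 h |
| Oesophagitis | <24 h | ≥24 h |
| Nausea | <24 h | ≥24 h |
| Vomiting | <24 h | ≥24 h |
| GI perforation | <24 h | ≥24 h |
| Diarrhoea | <24 h | <24 h |

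Five of the six change at the boundary and diarrhoea does not, so the row departs from the table's own pattern. The other criteria in the row still separate the grades: 4 to 6 extra stools a day against 7 or more, incontinence and hospitalisation at grade 3 only, moderate against severe ostomy output, and interference with daily activities absent against present. Only a case decided on IV fluids alone is unclear.

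**4. What the grade 2/3 boundary controls.**
- Reporting (section 11): grade 2 goes on the CRF only; grade 3 also needs an SAE form.
- Capecitabine/5FU modification (section 8.4.1): at first appearance, the next-cycle dose is 100% after grade 2 and 75% after grade 3; at second appearance, 75% and 50%. This applies to diarrhoea. Section 12.2 measures feasibility by the number of dose modifications and delays, so an inconsistent diarrhoea grade could carry into that count.
- Thrombosis: section 8.4.1 gives no thrombosis-specific step. Its cisplatin rules cover haematological, renal and neuro- or ototoxicity.

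**5. Scale.** No error rate can be derived. As an illustration only, if the rate of one DVT in 31 carried over, 90 × 1/31 ≈ 2.9, or about three per arm in Stage 1. A single event supports no more than an order of magnitude.

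**The case against.** The strongest reply is that the appendices are aids, not the standard. Sections 8.4.1, 11 and 12.2 all name CTCAE v3.0 itself, and Appendix XI says that it is a selection and links to the full list. A treated DVT can therefore be graded from the full criteria. The RTOG acute criteria are likewise named as an instrument, so a wrong appendix number does not make them unavailable. Mucositis, the toxicity singled out for the 60-patient review in section 12.4, has distinct grades in Appendix XI, as do oesophagitis and dysphagia.

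This stands as a limit on the consequence. A reader might infer that Stage 1 toxicity grades will be wrong, that every treated DVT is ungradable, that any diarrhoea with short IV fluids could be either grade, or that thrombosis grading alters dosing. The documents support none of these: the full standard governs, the diarrhoea row has other separators, there is no thrombosis dose step, and no misgraded entry is shown.

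A second reply is that the two Appendix XI cells might be faults of text extraction; in Appendix XII, for instance, the kidney row repeats the bladder row. That cannot be excluded from the text alone, and it is a reason to check the original pages first. It does not touch the acute/late mismatch.

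The defects remain. A link to the full standard does not repair a faulty table handed to sites for filling in CRFs, and nothing in the protocol supplies the acute RTOG scale.

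**Conclusion.** The point holds as a matter of inconsistent grading rules. The acute/late mismatch is certain. The identical thrombosis cells and the repeated diarrhoea limit are errors in the table as it reads here, subject to a look at the original pages.

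The effect is confined to RTOG acute scoring, which has no correct table in the protocol, and to two CTCAE rows, where sites relying on Appendix XI may differ at the grade 2/3 boundary. For thrombosis, both untreated and treated DVT are affected and the consequence is SAE-form reporting. For diarrhoea, only cases resting on IV fluids alone are affected, and the consequence is reporting and the capecitabine/5FU row.

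This assumes that some sites grade from the appendix rather than from full CTCAE v3.0; the protocol invites that but does not show how often it happens. The correction should be made, because it is cheap and toxicity informs the decision to continue.

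**What to change.** 1. In section 12.2, supply or cite the RTOG acute criteria for treatment visits, and state that Appendix XII applies to late effects at follow-up. Give the Stage 2 paragraph the same references.
2. Check the thrombosis and diarrhoea rows of Appendix XI against CTCAE v3.0 and correct them.
3. Before the Stage 1 IDMC review, query any thrombosis entries, and any diarrhoea entries graded on IV fluids alone, so that they are graded on one basis.

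The cost is a replacement appendix, a note to sites and a small data query. No dose or clinical rule needs to change.

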### 1.2 Abstract and summary of trial design

SCOPE 1 is a two arm, open, randomised Phase II/III trial. Eligible patients will have histologically confirmed carcinoma of the oesophagus (squamous cell, adenocarcinoma, or undifferentiated carcinoma) and have been chosen to receive definitive chemoradiotherapy (CRT) by an accredited multidisciplinary team (MDT) including a specialist Upper GI surgeon. 420 patients will be randomised to receive definitive CRT with or without cetuximab using a 1:1 ratio (210 patients per arm).

During the first stage (Stage 1) of the study, the trial will assess toxicity (unexpected and expected), activity and feasibility in 90 patients in the experimental arm. Activity will be measured as treatment failure-free rate and feasibility as the number of protocol dose modifications and delays. If toxicity, activity and feasibility are found to be unacceptable recruitment into the trial will stop. If the experimental arm is found to be active, safe and feasible, by the Independent Data Monitoring Committee (IDMC), recruitment will continue into the second stage (Stage 2) of the study. Stage 2 of the study will recruit a further 120 patients into each arm (a total of 420 patients) and compare the overall survival of both groups. The experimental arm of chemo-radiation and cetuximab will be compared against the control arm of chemo-radiation alone. This second stage of the trial is powered to detect a survival advantage with the addition of cetuximab.

All patients randomised into Stage 1 will contribute to the Stage 2 comparison of overall survival. In addition to overall survival, Stage 2 of the study will also assess toxicity, quality of life (QoL) and health economics.

Detailed radiotherapy treatment protocols have been notably absent in recent UK Upper GI Cancer trials involving chemo-radiation, as have procedures to assess adherence to

treatment recommendations. Therefore a detailed radiotherapy protocol and quality assurance procedure will be incorporated in this trial.

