| Oesophagus | Definitive
CRT         | 31 | 18:13     | 9 (29)
G3 PPE x 3
G3 Mucositis x 5
G3 Neutropenia x 1
1 x DVT | 4 x dose reductions
4 x dose delay
2 x treatment
discontinued –PD
1 x treatment
discontinued –IHD |
| Stomach    | Post-
operative
CRT | 7  | 7:0       | 2 (29)
G3 neutropenia x 1
G3 PPE x 1                                |                                                                                                                  |

Abbreviations: PPE, Palmar-plantar erythema; DVT, deep vein thrombosis;  
PD, progressive disease; IHD, Ischemic Heart disease.

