| 
Grade 2
Rash; flushing; urticaria;
dyspnoea; drug fever ≥ 38°C
                                                                                                   | 
Stop cetuximab infusion.
Administer bronchodilators, oxygen etc. as medically indicated.
Resume infusion at 50% of previous rate once allergic/hypersensitivity reaction has resolved or decreased to grade 1 in severity, and monitor closely for any worsening.
Cetuximab infusion time can be increased to a maximum of 4 hours; the infusion time will remain prolonged for subsequent infusions.
 
If patient has a second reaction on this prolonged infusion rate, the infusion should be stopped and not reintroduced.
This second reaction must be reported as a serious adverse event.
 |
| 
Grade 3: Symptomatic
bronchospasm, with or without
urticaria; parenteral
medication(s) indicated;
allergy-related
oedema/angioedema;
hypotension
 | 
Stop cetuximab infusion immediately and do not reintroduce.
 
Administer adrenaline, bronchodilators, antihistamines, glucocorticoids, intravenous fluids, vasopressor agents, oxygen etc., as medically indicated.
 
This must be reported as a serious adverse event.
                                                                                                                                                                                                                                                                                                                                     |
| 
Grade 4: Anaphylaxis
                                                                                                                                                     | 
Patients have to be withdrawn immediately from treatment and must not receive any further cetuximab treatment.
 
This must be reported as a serious adverse event.
                                                                                                                                                                                                                                                                                                                                                                                                                                               |

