### **10.9.1 Withdrawal from trial treatment**

A patient may withdraw, or be withdrawn, from the treatment protocol for the following reasons:

- a) Intolerable adverse effects as judged by the Investigator or the patient.
- b) Patient decision to discontinue treatment.

- c) Any patient whose treatment is delayed for longer than 3 weeks due to drug treatment related toxicity should discontinue therapy. Treatment delay for radiotherapy should be not be longer than 2 weeks.
- d) Serious systemic allergic reaction to any of the study drugs e.g. angio-oedema, anaphylaxis.

The reason should be recorded on the treatment form and the withdrawal form.

In such cases patients will be clinically managed as deemed appropriate by their supervising clinician, but such treatment would not be expected to include cetuximab which is considered as an experimental treatment in this disease.

The patient should however remain in the trial for the purposes of follow up and data analysis and follow up CRFs should be returned to the WCTU.

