### 12.3 Sample size calculation

#### Stage 1:

The treatment failure-free rate in patients treated with CRT is approximately 60% at 24 weeks. With the addition of cetuximab it is felt that a treatment failure-free rate of less than 60% would not be sufficiently large enough to warrant further investigation in a Phase III setting, but that a rate of 75% or higher would warrant further investigation. Using a Fleming's single stage design,  $p_1=0.60$  and  $p_2=0.75$ , setting  $\alpha=0.05$  and 90% power 83 patients would be required. To allow for 10% not being assessable and with a 1:1 allocation 90 patients will be recruited into each arm, a total of 180 patients. The IDMC will review the treatment failure-free rate, along with toxicity and feasibility, before they endorse continuation into Stage 2.

#### Stage 2

Calculations were performed using the ART package in Stata 9 assuming a 3 year recruitment period followed by 1 year of follow up (based on a 2-sided log rank test). The 2 year overall survival rate in patients treated with CRT is approximately 35%. In order to detect an improvement in 2 year overall survival from 35% to 47.5% (Hazard Ratio [HR] =0.71) with 80% power at a 5% significance level a total of 420 patients (269 events) are required. A total of 210 patients will be recruited to each arm.

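### Stage 1 feasibility is defined only as a count of dose changes and delays, which does not measure whether the planned treatment was delivered

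*Protocol*

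**What the plan says.** Section 12.2 lists feasibility as a secondary outcome of Stage 1 and says that it "will be measured through the number of protocol dose modifications and delays". Section 1.2 has the same definition: "feasibility as the number of protocol dose modifications and delays". Neither place mentions treatment completion, permanent discontinuation, dose received or a denominator.

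The outcome has a role in the continuation decision. Section 1.2 states: "If toxicity, activity and feasibility are found to be unacceptable recruitment into the trial will stop". Section 12.3 states: "The IDMC will review the treatment failure-free rate, along with toxicity and feasibility, before they endorse continuation into Stage 2". There is no formal comparator; the note closing section 12.2 begins "Although activity, safety and feasibility will not be formally assessed in the control arm in Stage 1".

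Several routes lead off treatment. Section 10.9.1 lists intolerable adverse effects, the patient's own decision, serious systemic allergic reaction, a radiotherapy delay of more than 2 weeks, and this rule for drugs: "Any patient whose treatment is delayed for longer than 3 weeks due to drug treatment related toxicity should discontinue therapy". For a grade 3 hypersensitivity reaction, section 8.4.2 states: "Stop cetuximab infusion immediately and do not reintroduce". The capecitabine schedule in 8.4.1 ends in permanent discontinuation after repeated toxicity.

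**The concern.** Dose changes and delays can occur only while a patient is on treatment. Once an agent is stopped, it contributes no further events. A patient whose cetuximab ends with a grade 3 reaction during the first infusion scores 0 or 1 for that drug. A patient who completes all 12 weeks with three short interruptions scores 3. By this measure the second patient looks the harder to treat, although that patient received the regimen and the first did not receive its experimental part.

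At stake is the information before the IDMC when it decides whether the trial goes on to recruit the further 240 patients of Stage 2. Whether most patients can get through the combined regimen is a central feasibility question, and the defined measure does not answer it.

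**Working it through.** The protocol gives no feasibility figure, so there is none to reproduce. The check has two parts.

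**1. Does a permanent stop count as a modification?** The text points both ways.

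- For counting it: all of section 8.4 is titled as dose modifications and contains stopping rules for cisplatin, capecitabine and cetuximab. In Table 1 (section 2.3) the discontinuations stand beside "4 x dose reductions" in a column whose heading covers dose modifications together with treatment interruptions.
- Against: the title of 8.4.2 names the stopping criteria separately from the dose modifications.
- Outside either reading: withdrawal by patient decision (10.9.1, item b) does not arise from any rule in 8.4.

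Both readings are therefore carried through below.

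**2. What does the count do when patients stop?** From the protocol: 90 research-arm patients in Stage 1 (12.3) and 12 planned weeks (6.1). Assumed, because the protocol gives no values: λ events per patient-week on treatment (0.05, 0.1 or 0.2), a fraction q of patients who stop (40%), and the week w after which they stop all agents (3 or 6). Stoppers and completers are given the same λ while on treatment.

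- Patient-weeks: T = 90 × [(1 − q) × 12 + q × w]
- Expected count, stops left out: λT
- Expected count, each stop counted once: λT + 90q

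Full completion: T = 90 × 12 = 1080. With 40% stopping after week 6: T = 54 × 12 + 36 × 6 = 864. With 40% stopping after week 3: T = 54 × 12 + 36 × 3 = 756. In both stopping scenarios 54 of 90 complete, and 90q = 36.

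| λ | All 90 complete | Stop wk 6, stops left out | Stop wk 6, stops counted once | Stop wk 3, stops left out | Stop wk 3, stops counted once |
|---|---|---|---|---|---|
| 0.05 | 54 | 43.2 | 79.2 | 37.8 | 73.8 |
| 0.1 | 108 | 86.4 | 122.4 | 75.6 | 111.6 |
| 0.2 | 216 | 172.8 | 208.8 | 151.2 | 187.2 |

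With stops left out, the count falls by 20% (864/1080) or 30% (756/1080), whatever λ is.

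With each stop counted once, the change from full completion is 90q × [1 − λ(12 − w)]. It is positive for small λ, negative for large λ, and zero at λ = 1/(12 − w). That is 1/6 = 0.167 for w = 6 and 1/9 = 0.111 for w = 3, or 2.0 and 1.33 events per patient over a full 12 weeks. At those rates the expected count is the same whatever fraction of patients stops.

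**The case against.** The strongest opposing case is that stops are already inside the measure. Section 8.4 and the Table 1 column heading both place them with dose modifications. Many patients who stop for toxicity will also have been counted beforehand: under the capecitabine schedule, permanent discontinuation comes at the fourth grade 2 appearance, after three interruptions, or at the third grade 3 appearance, after two. A stop for a delay beyond 3 weeks is itself a delay. Stopping one agent does not end the count for the others, and section 9.5 asks that radiotherapy continue where possible. In addition, the IDMC sees toxicity and activity, withdrawal reasons are recorded, and denominators are ordinary content for the analysis plan promised in 12.5.

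Much of this stands, and it rules out two stronger readings. A reader might infer that the measure runs backwards, so that poor tolerability always lowers the count and biases the decision towards continuing. The documents do not support that: with stops counted once, the illustration gives a higher count at two of the three assumed rates. A reader might also take from Table 1 that 3 of 11 delivery events (27%) fall outside the measure. The column heading does not support that either, and two of those three stops were for progressive disease rather than tolerability.

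The objection leaves three things untouched. Withdrawal by choice is outside 8.4. A permanent stop carries at most the weight of a brief delay. And the protocol itself chooses the measure: an analysis plan can add a denominator, but one that follows this definition still has no term for completion or dose received. That the IDMC might notice early stopping from other data does not repair the stated criterion.

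**Conclusion.** The point holds in a limited form. As defined, feasibility does not measure delivery of treatment and can fail to distinguish a regimen that many patients abandon from one that nearly all complete. In the illustration, with 54 of 90 completing instead of all 90, the count ranges from 30% lower (stops left out, week 3) to 47% higher (79.2 against 54; stops counted once, week 6, λ = 0.05), and it can also be almost unchanged (111.6 against 108).

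These figures rest on assumed event rates, on stoppers leaving all agents together, and on equal event rates before stopping. If only one agent is stopped, the loss of events is smaller. If stoppers have more events beforehand, the count is higher. The documents support neither a fixed size nor a fixed direction. Because feasibility is secondary, has no numerical threshold and is read alongside toxicity and activity, this is a cheap improvement to the Stage 1 decision and not an error that invalidates it.

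**What to change.** In sections 1.2 and 12.2, define feasibility among all patients allocated to the research arm as:

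- (a) the proportion completing planned treatment, separately for radiotherapy, cisplatin, capecitabine or 5FU, and cetuximab, with permanent discontinuation for any reason counted as not completed;
- (b) the percentage of the planned dose received, for each agent.

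Report modifications and delays per patient or per cycle started, as supporting description, and say whether a permanent stop is included in that count.

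The cost is a change of wording and slightly more tabulation. Medication compliance is already confirmed on the CRF (10.1), reasons for stopping go on the treatment and withdrawal forms (10.9.1), and radiotherapy plan and dose data are collected for each patient (17.5). It should be confirmed that delivered fractions are recorded as well. The reported feasibility may look less favourable. No dose, schedule or stopping rule changes.
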